### Measurement methods

#### Description of data forms

Table
2 describes the data forms that will be used for this study:

**Table 2 T2:** Data forms

**Form #**	**Form title**	**Description**	**Completed by**
FA00	Sampling and Initial Recruitment Log Form	Documents the outcomes of searching the clinical records for potentially eligible subjects and of initial contacts with potentially eligible subjects including their interest in participation in the study.	Clinical Coordinator
FA01	Contact Form	Documents contact information for each potentially eligible subject and updated contact information for participating subjects.	Information extracted initially from clinical records and reviewed/updated with potentially eligible subjects and participating subjects by the Clinical Coordinator.
FA02	Screening Form	Documents eligibility for participation for each study subject selected.	Clinical Coordinator
FA03	Enrollment Form	Documents marital status, information about children, and smoking, alcohol use, menstruation, contraception and gynecological care of the study subject.	Clinical Coordinator
FA04	Enrollment Confirmation Form	Records blood test results, and study medication delivery to the subject, and plans for follow-up visit. This form may not need to be completed with the subject at some sites as all the information will be available to the Clinical Coordinator.	Clinical Coordinator.
FA05	Follow-up Form	Confirms address information, documents menstruation, administration of study medication, and plans for next follow-up visit.	Clinical Coordinator
FA06	Initial Prenatal Contact Form (With Study Subject)	Documents date of last menstruation, date of pregnancy confirmation, and information about the study subject’s doctor and source of prenatal care.	Clinical Coordinator
FA07	Prenatal Form (With Doctor)	Documents via periodic contacts with the subject prenatal care provider, or via abstraction from prenatal care records, information about the study subject’s pregnancy, prenatal vitamins, illness, ultrasound results, etc.	Co-Principal Investigator (initial contact),Clinical Coordinator
FA08	Study Continuation Post Miscarriage/Stillbirth Form (With Study Subject)	Collects data from the subject about her readiness to resume participation in the study after a miscarriage/stillbirth occurrence and arrange for the date and time of the next visit if she is willing to continue in the study.	Clinical Coordinator
FA09&10	Miscarriage/Stillbirth Form (With Doctor)	Documents the miscarriage or stillbirth date and age, as well assessment of miscarriage/still birth product if available including the presence or absence of clefting and other malformations, etc.	Co-Principal Investigator, Clinical Coordinator
FA11	Delivery Form (With Subject)	Documents date of delivery, birth weight and sex of the infant, mother’s smoking and drinking habits while pregnant, and any complications and malformations associated with the baby.	Clinical Coordinator
FA12	Delivery Form (With Doctor)	Documents any malformations that may be associated with the baby including craniofacial malformations and abnormal delivery events. Filled with the subject’s doctor (if possible) or abstraction from the medical records of the subject.	Clinical Coordinator
FA13	Phone Call Form	Documents telephone calls made to the study office by the study subjects, the reason for each call, and the action taken.	(Clinical Coordinator, Co-Principal Investigator)
FA14	Study Termination Form	Documents withdrawal from the study by a study subject, the reason(s) for termination and approval (or not) for a two-month post termination follow-up.	Clinical Coordinator
FA15	Post Termination Follow-up Form	Confirms address information, documents menstruation and whether or not the former study subject has gotten pregnant.	Clinical Coordinator
FA16	Laboratory Form	Documents the date of blood collection, date of analysis, and results of the blood testing.	Clinical Coordinator
FA17	Adverse Events Form	Documents all information related to any adverse event encountered during the course of the study.	Clinical Coordinator/Co-Principal Investigator
FA18	Protocol Violations Form	Documents all information related to any protocol violation encountered during the course of the study.	Clinical Coordinator/Co-Principal Investigator
FA19	Pregnancy Confirmation Form	Documents the results of a performed pregnancy test after randomization and related schedule of study folic acid supplementation	Clinical Coordinator
FA20	Prenatal Form (With Subject)	Documents via periodic contacts with the subject, information about pregnancy progress, prenatal vitamins, illness, ultrasound results, smoking/alcohol etc.	Clinical Coordinator
FA21 and FA21 Suppl-ement	Delivery Form (In-Person Evaluation of Live Birth	Documents the presence or absence of malformations and/or complications with birth upon in-person evaluation of the live born by the Clinical Coordinator.	Clinical Coordinator or Co-Principal Investigator and clinical geneticist (or pediatrician)
FA22 (Outreach-model only)	Pre-Contact Form	Documents the outcome of each attempt to contact subject by the study staff or voluntary professionals assisting on the study.	A study team member, Social worker, Parent Coordinator

#### Description of biological measures

The following laboratory measures will be collected from the subjects found in Table
3.

**Table 3 T3:** Laboratory measures

**Laboratory measure**	**Timing**	**Aim**	**Performed by**
Complete blood count	At baseline, every 12 months post initiation of supplementation, and at pregnancy confirmation.	Anemia	Laboratory of study clinic
Pregnancy test	Whenever menstrual delay of 14 days or more is detected	Pregnancy	Laboratory of study clinic or an outside affiliated laboratory
Folate analysis	At baseline, every 12 months post initiation of supplementation, and at pregnancy confirmation.	Measure serum/red cell folate concentration	Laboratory of study clinic or an outside affiliated laboratory
Vitamin B12 analysis	At baseline and every 12 months thereafter	Detect pernicious anemia	Laboratory of study clinic or an outside affiliated laboratory

The following physical exam measures of babies born to subjects will be abstracted from medical records:

Birth defects

Birth weight

Length

Head circumference (when available)

The Clinical Coordinator will also obtain and document information on the presence of craniofacial malformations including clefts or other birth defects in babies born through personal evaluation of the infant, contact with the subject’s doctor after delivery, or abstraction from the medical record of the infant, but the clinical coordinator will make every attempt to evaluate in person every infant born into the study. Information about any malformations detected during the prenatal period through ultrasound testing will also be obtained from contact with the subject, her prenatal care provider, or through abstraction from the prenatal care record.

#### Schedule of data collection

Data will be collected during the various stages of subject sampling, screening, enrollment, follow-up, pregnancy occurrence and progress, and termination from study. General contact information (name, telephone, number, etc.) will be documented prior to introducing the potential subject to the study when possible. This information (telephone, residence, name, etc.) will be verified upon initial contact with the subject. Data will also be documented when screening willing subjects, which will occur either directly or within a week period after first contact with the subject. Data will also be collected during enrollment of eligible subjects, which will occur either directly or within a week period after screening, and during each bi-monthly follow-up. Upon occurrence of pregnancy, data will be collected through contact with subject and/or subject prenatal care provider and/or through abstraction from the medical record. The subject will be contacted at an appropriate time after pregnancy resolution, regardless of the pregnancy outcome, to obtain information on study outcomes and check on her willingness to resume participation in the study. Standard enrollment, data collection, and follow-up procedures will be followed with study subjects who agree to resume participation in the study. A study termination form will be completed with subjects who wish not to resume participation in the study, and a follow-up visit is conducted after two months, whenever possible, to check on pregnancy occurrence and source of prenatal care if subject is pregnant and obtain permission to contact her provider to inquire on her pregnancy.

Tables
4 and
5 below include schedules of data collection, procedures performed, data forms completed, and laboratory tests conducted before and after detection of a delay in menstruation respectively.

**Table 4 T4:** Schedule A (Data collection before any detection of a menstruation delay)

**Task**	**Timing**	**Procedure**	**Forms**
Abstraction from clinical record	Sampling phase	Search clinical records to identify potentially eligible subjects	FA00
Introduction to study	First contact with subject (in person or by phone)	-Verify potential eligibility	FA00
		-Verify subject address and contact information	FA01
		-Introduce potential subject to the study	
		-Explain study purpose and subject responsibilities	
		-Answer any questions that potential subject may have	
		-Check willingness of potential subject to participate	
Screening	Directly or within a week period after introduction into study	Screen subject for eligibility	FA02
Enrollment	Directly or within a week period after screening	-Obtain informed consent	FA03
		-Obtain blood sample from subject	
		-Inform subject of process of study drug dispensing and next follow-up	
Verification of B12 and pregnancy test results, randomization, dispensing study pills, and baseline contact	Within 1–2 weeks days after enrollment	-Verify blood test results (mainly B12 levels)	FA04
		Randomize subjects who have no B12 deficiency and are not pregnant and dispense folic acid pills	
		Refer subjects who have B12 deficiency to hematology service	
Follow-up onward	Every 2 months (about 8 weeks)	-Dispense and confirm receiving folic acid pills	FA05
		-Complete follow-up visit form	
Follow-up when blood sampling is due	(Once every 12 months after enrollment.	-Schedule an in person follow-up for blood sampling	FA05
		-Dispense folic acid pills	FA16
		-Complete follow-up visit form	

**Table 5 T5:** Schedule B (Data collection after detection of menstruation delay or pregnancy)

**Task**	**Timing**	**Procedure**	**Forms**
Verification of pregnancy and measuring folate levels (if pregnant).	- Whenever delay in menstruation of 14 days or more or pregnancy are identified at either at bi-monthly follow-up or contact with subject between follow-ups	- Request that subject completes a pregnancy test within a week after detection of menstruation delay if pregnancy is not confirmed (For clinic based model, pregnancy can be tested for at study clinic).	- FA19 to document pregnancy test result
		- Schedule an in-person follow-up within a week after confirming pregnancy (if subject is not in clinic when first confirmed). An in-person follow-up in this case is only required if pregnancy occurs before the end of first year post initiation of supplementation and blood sampling is required for folate measurement.	- FA16 to document folate level
		Obtain blood samples for a folate testing (if applicable).	- FA06 (if pregnancy is confirmed)
		- If pregnancy is confirmed, calculate gestational age and advise subject as when to stop taking the study pills	
		- If subject is not pregnant, then proceed with the regular follow-up and supplementation schedule for non-pregnant subjects	
Prenatal follow-up with subject	Bimonthly follow-up during pregnancy	Contact subject to inquire on pregnancy progress and subject health status	FA07 supplement
Prenatal follow-up with doctor	Monthly follow-up during pregnancy	Contact subject’s prenatal care provider or abstract from prenatal care records to monitor pregnancy events	FA07
Follow-up after miscarriage/stillbirth occurrence	Within 60 days of Miscarriage/Stillbirth	- Check willingness of subject to resume participation in the study	- FA08
		- Contact subject’s doctor (if possible) to obtain information about miscarriage/stillbirth event and material	- FA09&10
		- Check the presence of clefting	- FA13
		- Photographic documentation	
		- Complete study termination form if subject is unwilling to continue in the study	
Follow up after delivery (live birth)	Within 60 days of delivery date	- Check delivery events, maternal health behavior during pregnancy, and infant health measures with study subject; check subject’s readiness to resume enrollment in the study	- FA11
		- Evaluate the infant in person to check for presence of craniofacial or other malformations.	- FA12
		- Complete study termination form if subject is unwilling to continue in the study	- FA21 and FA21 Supplement
		- Contact subject’s doctor (if possible) or review medical records to check the presence of craniofacial malformations including clefting and other defects as well as delivery complications; - Photographic documentation	- FA13
Post-termination follow up	Two months after termination from study	Determine whether the subject became pregnant and request consent to contact her prenatal care provider	- FA14
- Screening and enrollment	After subject agrees to resume enrollment in the study	- Follow standard screening, enrollment procedures listed above	- FA02
- Verification of B12 and pregnancy, dispensing study pills, and Baseline contact		- Subject remains in the original randomization group	- FA03
			- FA04

#### Administration of data forms

Research staff will administer and complete the data collection forms being used for this study using pencil and paper format in primary subject language (Portuguese). Subjects will also self-complete mailed follow-up forms in the outreach model. Research staff will transcribe completed data forms to the study database.

#### Collection of biological samples/shipping

Each blood sample will consist of 4–12 millimeters of peripheral venous blood collected from the subject. Blood will be collected by the Clinical Coordinator or other qualified staff in vacuum tubes either containing anti-coagulant (1.5 ml) or not. All blood collection tubes will be identified by date, name, and subject ID number. Blood samples will be delivered to the laboratory to be analyzed. Blood samples obtained during follow-up outside of the clinic (such as at subject home) will be stored in portable freezers before being delivered to the laboratory.

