#### Secondary hypotheses

The following secondary hypotheses will be evaluated:

An increase in serum and/or red cell folate levels in all women following daily supplementation with folic acid.

When compared to the 0.4 mg supplemented groups, the 4 mg per day group will have the following:

‐Greater increases in serum and/or red cell folate.

‐Decreases in the recurrence of NSCL/P in each of the following subgroups:

•Women with NSCL/P themselves

•Women with one or more children with NSCL/P

‐A decrease in the severity of NSCL/P in offspring of trial mothers.

‐No increase in twinning rates.

No increase in miscarriage rates.

No increase in rates of preeclampsia.

‐No increase in rates of other birth defects.

‐No decrease in birth weight

‐No decrease in gestational age

A decrease in recurrence of NSCL/P in the group of study subjects compared to an historical control group obtained from the populations served by the craniofacial clinics participating in the study.

A greater decrease in the recurrence of NSCL/P in the group of study subjects receiving 4 mg of folic acid when compared to the historical control group relative to that of the group receiving 0.4 mg when compared to the same control group.

Under separate funding we will examine the role of genes involved in folate metabolism on folate, B12 and homocysteine levels, as well as potential interaction between these genes and the supplementation dose. This project will also establish a resource to examine the long-term outcomes of infants exposed to high dose folic acid in utero.

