#### Enrollment and baseline data collection

Once screened, the Clinical Coordinator will enroll eligible subjects who provide informed consent. The Clinical Coordinator will complete the enrollment form, and will obtain a blood sample (about 8 ml) from the subject for baseline measures of RBC, hemoglobin, B12, and serum/RBC folate.

Blood samples will be analyzed at a maximum of 2 weeks. Enrollment of subjects with normal B12 levels will be confirmed. Subjects found to be B12 deficient will be referred to a hematologist for treatment, and will be excluded from participation.

The Clinical Coordinator will randomize each confirmed subject into the 0.4 and the 4 mg folic acid groups (see section 3.6) and will dispense the folic acid pillbox with the relevant pillbox ID number. Study pills will be sent to randomized subjects by mail in most cases; subjects with unreliable addresses or who frequently attend the clinic for care receive their pills at the clinic. When delivered by mail, the clinical coordinator will contact the subject by phone to confirm their receipt of the pillbox.

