#### Blood collection

Folate (Serum and RBC) levels will be assessed, at baseline (prior to supplementation), every 12 months after enrollment, and at pregnancy. B12 levels will be assessed at baseline and subsequently every year to monitor for B12 deficiency. Folate and B12 tests may be conducted at the own laboratory facilities of the clinic/hospital when available or alternatively at local laboratories determined by the Co-Principal Investigator. The Clinical Coordinator and Co- Principal Investigator will monitor B12 levels and will refer subjects with B12 deficiency to the hematology service for treatment. Randomized subjects found to be B12 deficient may be temporarily or permanently suspended from the study drug based upon recommendations of the hematology referral.

Based on clinical and research experience, few subjects (perhaps none) are expected to ask for their blood results. If requested prior to the end of the study, an independent physician serving in the clinic will provide confidential results to the subject. The subject will also have the opportunity to discuss what her results mean (in terms of being within normal range or not) with the physician independently from other study subjects and research unit staff. This procedure will prevent sharing the results with other study participants as well as with any member of the research team. Since no data is available on what these folate measurements will actually mean in terms of the levels of folic acid supplementation that are provided, it would be impossible for any single woman to interpret these data points in a way that could result in her un-blinding. Therefore, any disclosure of folate test results under these specific circumstances will not affect the blinding of study subjects or of research unit personnel.

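### Off-site follow-up blood goes into portable freezers before reaching the laboratory, which, read literally, defeats the scheduled blood count and, unless serum is separated first, inflates serum folate

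*Protocol article*

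**What the plan says.** The section on collection of biological samples and shipping has venous blood drawn "in vacuum tubes either containing anti-coagulant (1.5 ml) or not". For follow-up draws made away from the clinic, for example at the woman's home, it adds that they "will be stored in portable freezers before being delivered to the laboratory". It gives no storage temperature and mentions no centrifugation, serum separation or cell count before that step. The short section on laboratory analysis only points back to Section 3.

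Table 3, under the description of biological measures, schedules a complete blood count, with anaemia as its aim, "At baseline, every 12 months post initiation of supplementation, and at pregnancy confirmation". It assigns the count to the laboratory of the study clinic. The folate row has the same timing and the aim "Measure serum/red cell folate concentration". The Blood collection section agrees: "Folate (Serum and RBC) levels will be assessed, at baseline (prior to supplementation), every 12 months after enrollment, and at pregnancy".

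The first secondary hypothesis is "An increase in serum and/or red cell folate levels in all women following daily supplementation with folic acid". A second one expects a larger rise with 4 mg than with 0.4 mg.

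For enrolment, the only handling rule is a time limit: "Blood samples will be analyzed at a maximum of 2 weeks". Item 6 of the Research Unit's duties mentions processing field samples and preparing them for folate, without saying what that involves or when it is done.

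**The concern.** A blood count needs intact cells, and frozen whole blood no longer has them. Folate is also far more concentrated in red cells than in serum, so lysis before separation moves red-cell folate into the fraction measured as serum. The stated order is collection, freezer, laboratory, and the laboratory is where Table 3 has the count done.

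Two things are at stake. One is the before-after folate comparison: if a woman's baseline was separated unfrozen and her follow-up was frozen as whole blood, serum folate would appear to rise even if she took no pills. The other is the repeat anaemia check in Table 3 for women whose follow-up blood is drawn off-site.

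**Working it through.** No sample size, power or alpha figure depends on this point, so there is no stated figure to reproduce. The check sets the sections side by side and then illustrates the size.

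**1. Order of steps, by assay, for an off-site follow-up sample**

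- *Blood count and haematocrit.* The count is done in the laboratory and the freezer comes before the laboratory. The count is lost unless a separate anticoagulated tube stays unfrozen, and none is mentioned. This holds even if serum is separated in the field.
- *Serum folate.* Valid if serum is separated before freezing, contaminated if it is not. The text does not settle which.
- *Red-cell folate.* Can be assayed on a frozen lysate, but conversion to a red-cell concentration needs the haematocrit.

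**2. Size of the serum error (illustration)**

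Inputs, all assumed because the documents give none: haematocrit H, red-cell to serum folate ratio k, fraction of red cells lysed f. By simple mixing,

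measured / true serum folate = [(1 − H) + f·H·k] / [(1 − H) + f·H].

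At H = 0.40 and k = 20:

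- f = 1%: (0.60 + 0.08) / 0.604 = 1.13
- f = 5%: (0.60 + 0.40) / 0.62 = 1.61
- f = 100%: (0.60 + 8.0) / 1.0 = 8.6

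Over H from 0.36 to 0.44 and k from 10 to 40:

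| Cells lysed | Measured / true |
|---|---|
| 1% | 1.05 to 1.30 |
| 5% | 1.25 to 2.47 |
| 100% | 4.2 to 18.2 |

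Whole-blood freezing points towards the last row. The first two show how little lysis is enough to matter.

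**3. What this does to a before-after change**

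Take assumed true values of 15 ng/ml in serum and 500 ng/ml in red cells, unchanged from baseline to follow-up, with H = 0.40. A clean baseline reads 15. With 5% lysis the follow-up reads (0.60 × 15 + 0.05 × 0.40 × 500) / 0.62 = 19 / 0.62 = 30.6. With complete lysis it reads 0.60 × 15 + 0.40 × 500 = 209. The apparent rise is then entirely an artefact of handling.

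**4. Red-cell folate without a haematocrit**

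Whole-blood folate is W = H·R + (1 − H)·S, so R = [W − (1 − H)·S] / H. With W = 209 and S = 15, a true H of 0.40 returns R = 500. Guessing 0.36 gives (209 − 9.6) / 0.36 = 554; guessing 0.44 gives (209 − 8.4) / 0.44 = 456. Red-cell folate is then only approximate, about −9% to +11% in this example, and less damaged than serum.

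**5. Who is affected**

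The freezer rule covers only follow-up samples taken outside the clinic. The documents do not say how many there will be.

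**The case against.** The strongest reply is that a condensed article leaves sample processing to the Manual of Operations, which is not shown, and that the Research Unit's duties already include preparing field samples for folate. Separation before freezing may therefore be standard practice here, and portable freezers may loosely mean cool boxes. This stands as far as serum folate goes: absence of a separation step cannot be proved. It does not rescue the blood count, because the article states a rule and that rule puts the freezer before the laboratory. If cool boxes were meant, the wording still needs correcting.

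A reader might infer several stronger things that the documents do not support:

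- *That the dose comparison is masked.* Handling is not said to differ by blinded arm, and the contaminant is red-cell folate, which is itself expected to rise more with 4 mg. With assumed serum/red-cell pairs of 5/200, 15/500 and 30/800 ng/ml at H = 0.40, complete lysis gives 83, 209 and 338: the order is kept. Serum values are distorted, but loss of the contrast is not shown.
- *That about 19% of women are affected.* The outreach model supplies 1,000 of 5,368 new enrolees (18.6%), but it is a recruitment model. Its women are enrolled at community meetings, so their baseline may be a field sample too, and home visits are not confined to it.
- *That clinic samples are known to be unfrozen.* Clinic storage is not described.
- *That the B12 safeguard fails.* The Related risks section ties its blood test for anaemia to enrolment and relies on yearly B12 assays afterwards. Neither is shown to be affected.
- *That pilot folate values must be dropped.* Storage of pilot samples is not described.

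**Conclusion.** The point holds in a limited form. As written, the handling rule for off-site follow-up blood conflicts with the assays scheduled on that blood. The follow-up count and haematocrit cannot be obtained from a frozen sample, and exact red-cell folate needs a haematocrit read beforehand. Serum folate is inflated if serum was not separated first. The before-after folate hypothesis can be distorted where baseline was handled differently, and the Table 3 follow-up anaemia check is lost for these women.

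The qualitative conclusion rests on reading the freezer literally and, for serum folate only, on no prior separation. The multipliers rest wholly on assumed haematocrit, folate ratio and lysis; the number of samples concerned is unknown. Because the hypothesis allows serum or red-cell folate, part of it could survive on red-cell values. The primary outcome, power and alpha are untouched. It should be corrected because it concerns a secondary outcome and a scheduled safety test, and the correction is cheap.

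**What to change.** Amend the section on collection of biological samples and shipping as follows:

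- State the storage temperature for off-site samples.
- Transport the anticoagulated tube for blood count and haematocrit cooled, not frozen.
- Allow freezing only of separated serum, or of a lysate whose haematocrit has already been read.
- Use the same handling at baseline and follow-up.

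Add a field to laboratory form FA16 for handling and visible haemolysis. Flag any sample known to have been frozen as whole blood and leave it out of the serum-folate and blood-count analyses.

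The cost is a wording change, one form field, and cool boxes for the blood-count tubes. The small downside is that remote samples must reach a laboratory or centrifuge sooner.
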